## Abstract

**Background:**

Recent advances in hardware and software enabled the use of artificial intelligence (AI) algorithms for analysis of complex data in a wide range of daily-life use cases. We aim to explore the benefits of applying AI to a specific use case in transplant nephrology: risk prediction for severe posttransplant events. For the first time, we combine multinational real-world transplant data, which require specific legal and technical protection measures.

**Objective:**

The German-Canadian NephroCAGE consortium aims to develop and evaluate specific processes, software tools, and methods to (1) combine transplant data of more than 8000 cases over the past decades from leading transplant centers in Germany and Canada, (2) implement specific measures to protect sensitive transplant data, and (3) use multinational data as a foundation for developing high-quality prognostic AI models.

**Methods:**

To protect sensitive transplant data addressing the first and second objectives, we aim to implement a decentralized NephroCAGE federated learning infrastructure upon a private blockchain. Our NephroCAGE federated learning infrastructure enables a switch of paradigms: instead of pooling sensitive data into a central database for analysis, it enables the transfer of clinical prediction models (CPMs) to clinical sites for local data analyses. Thus, sensitive transplant data reside protected in their original sites while the comparable small algorithms are exchanged instead. For our third objective, we will compare the performance of selected AI algorithms, for example, random forest and extreme gradient boosting, as foundation for CPMs to predict severe short- and long-term posttransplant risks, for example, graft failure or mortality. The CPMs will be trained on donor and recipient data from retrospective cohorts of kidney transplant patients.

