The NephroCAGE consortium was initiated as a strategic lighthouse project supported by the national governments of Germany and Canada to combine medical and technical expertise to build a real-world demonstrator and evaluate the added value of artificial intelligence (AI) in a very specific medical use case from nephrology. It brings together worldwide excellence from transplant centers, academia, and industry from Germany and Canada to join forces as depicted in Figure 1. In total, 4 major clinical kidney transplant centers from both nations have contributed transplants to form the first-of-its-kind international NephroCAGE data set; it forms a longitudinal database of patient-level data from more than 8000 transplant cases over the past 2 decades. The NephroCAGE data set builds the foundation for detailed retrospective data analysis using AI learning techniques and the development of clinical prediction models (CPMs) for prospective identification of posttransplant outcomes of kidney transplant patients. With the help of the CPM predictions, clinicians are expected to improve the quality of care for future patients with kidney disease in Canada, Germany and worldwide by identifying individual patient risks even earlier than possible today.

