Immunological differences play a key role in the development of organ rejection reactions, which might lead to graft failure or even graft loss [11,12]. It has been proven that transplant patients sharing compatible serologic human leukocyte antigen (HLA) types with the organ donor have better outcomes compared to patients with incompatible HLA types [13]. Today, only a subset of HLA genes is considered for matching of immunological factors from donors and recipients. The HLA genes located on chromosome six are responsible for encoding of proteins that fold complex structures, so-called epitopes. Today, it is known that checking for HLA compatibility requires in addition to pure genetic information also the assessment of the protein’s 3D structure, which might trigger immunological response. However, current organ allocation algorithms in productive use include only very limited aspects of HLA compatibility, for example, number of mismatches per HLA, to reduce the immunological risk for graft rejection and donor-specific HLA antibodies [14,15]. Recently, new matching methods have been developed to optimize assessment of organ compatibility between donors and recipients incorporating more functional aspects, for example, on biological level and additional molecular specifics [16-18]. Selected methods showed improved precision in predicting immunological risk, some of them being also relevant for organ allocation [11,17,19,20].

The NephroCAGE consortium aims to show advantages of using molecular compatibility for matching of organ donors and recipients. Therefore, we aim to incorporate the latest research results on B cell and T cell epitope matching as a specific feature of our CPMs. Furthermore, we will investigate the applicability of tree-based machine learning (ML) algorithms such as random forest (RF) and Extreme Gradient Boosting as a foundation for the development of CPMs trained on real-world transplant data in nephrology.

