Therefore, access to high-quality real-world data is crucial to train and validate high-quality AI models for clinical use. At the same time, clinical data are considered as highly sensitive data, which typically cannot be exposed for training of AI models. The NephroCAGE consortium as the first of its kind has access to multicenter transplant data from 2 nations for the development of AI-based CPMs. One of our hypotheses is that AI-based CPMs combining both clinical and immunological data will lead to improved detection of patients at high risk for graft loss and rejection. Conversely, we will focus on data from patient follow-ups and immunological data, for example, presence of donor-specific antibodies (DSA) for HLA.

Over the past decades, hospitals and transplant centers have developed individual clinical information systems for management of their transplant patient data. As a result, data are scattered across multiple silos using various data formats, which makes multisite research a complex data management task. Thus, the use of standardized data formats, common data dictionaries, shared terminologies and ontologies, and open application programming interfaces (APIs) are required to facilitate the deployment and integration of innovative AI-based solutions into existing clinical IT systems.

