### Using ML for CPMs

Various related work showed that AI approaches based on medical input data can result in accurate and robust statistical models to predict patient outcomes [30-34]. For example, supervised tree-based ML algorithms, for example, RF and Extreme Gradient Boosting, have shown promising results for classification tasks for posttransplant risks, for example, for graft failure, patient survival, or graft loss within a certain time period [35-40]. However, most of the existing approaches were research-driven and had only limited access to real-world medical data for their work, for example, using the Scientific Registry of Transplant Recipients data set [41]. Loupy et al [42] developed a risk score for kidney transplant recipients in context of a multicenter study making use of multivariable Cox regression analysis to predict graft loss in patients. Among others, they incorporated the following features: estimated glomerular filtration rate, proteinuria, histology, and HLA antibody [42]. Furthermore, recently advanced approaches based on neural networks making use of large proteomic databases occurred for assessment of immunogenicity and probability to generate antibodies [27,43,44].

From a clinical perspective, NephroCAGE aims to prevent the occurrence of adverse posttransplant end points, for example, loss of function, graft failure, and patient death. Nowadays, regular monitoring is applied to help identifying individual risk factors as early as possible. The use of digital patient records in hospitals for more than a decade provides the data foundation for our work because they form a longitudinal database of historic patient cases, medical decisions, therapies, and disease progression. Today, historical case data are only rarely used for current patient care. Our research hypothesis is that the analysis of historical cases can help to derive prognostic predictions for the individual patient risk to reach severe clinical end points. Based on the analysis of patient-specific parameters, a current patient case will be assigned to a group of similar, historic patient cases.

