### NephroCAGE FLI

Figure 4 depicts the building blocks of the NephroCAGE FLI, that is, from bottom to top: local transplant data accessed by local FLI runtimes, a federation layer for exchange of CPMs and data, as well as AI-based model making use of the NephroCAGE FLI to support clinicians in gaining medical insights. Each NephroCAGE clinical partner will join the NephroCAGE FLI by installing and configuring a local NephroCAGE FLI runtime environment on a dedicated host. After transplant data have been extracted from local clinical systems and harmonized, the host running the local FLI runtime environment is granted access to the data. Afterwards, the training of CPMs can be performed on the local data set. Once a stable CPM version becomes available, it will be released for sharing between partners using the NephroCAGE FLI. As a result, pretrained CPMs can be exchanged via the NephroCAGE FLI to facilitate model training even across country borders.

We will use DLT such as an Ethereum blockchain network to have decentralized storage for communicating model updates and code between clinical transplant centers without the need for a dedicated central authority [54]. For support of model training, we will implement an institutional incremental learning approach, where members retrain models one after another and compare different collaborative learning mechanisms with each other [23]. The aggregation of model values is well-established for parameter-based approaches like neural networks. However, only limited research investigates the aggregation of tree-based or kernel-based approaches like RFs or support vector machines, which are relevant for the NephroCAGE use cases.

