We will work together with nephrologists and clinical experts to identify clinical end points of interest as basis for CPM development. We will start to investigate the applicability of tree-based models and artificial neural networks as ML methods based on our literature review, because tree-based methods perform better on imbalanced tabular data than neural networks. Furthermore, tree-based methods show better explainability by providing explicit feature importance. Finally, an imbalance of data in kidney transplantation might lead to over-fitting for the majority classes. Consequently, we will apply resampling methods to reduce this effect [58-60].

Genomic data for the HLA compatibility algorithm are among the most sensitive transplant data. Therefore, we aim to implement an anonymization client so that the HLA is not susceptible to various privacy threats. Today, only 5 genetic loci from HLA-A, -B, and -DR are used by Eurotransplant’s graft allocation algorithm despite a total of 11 clinically relevant HLA loci being associated with immunologic risk [15]. Molecular matching, such as PIRCHE, has been shown to provide additional value to serologic HLA matching in assessing risk of developing donor-specific HLA antibodies, thus having the potential to improve long-term transplant outcomes. Furthermore, donor-specific antibodies are a major factor for rejection that deteriorate organ function and result in graft loss. Although we will use the NephroCAGE FLI to share CPMs between partners, still concerns remain about the privacy of patient data in the case of backtracking the ML model coefficient into individual patient outcomes. Therefore, we will incorporate only deidentified data as basis for CPM training, that is, anonymization of sensitive attributes such as follow-up visit dates, surgery date, and birth date.

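### The stated aim is to evaluate the added value of AI, but the stated model comparison is among AI algorithms, so it can rank them but not show gain over a conventional model

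*Protocol article*

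**What the plan says.** Three statements set up a comparative question. The Abstract (Background) opens with "We aim to explore the benefits of applying AI to a specific use case in transplant nephrology: risk prediction for severe posttransplant events". The Introduction gives the purpose of the consortium as to "evaluate the added value of artificial intelligence (AI) in a very specific medical use case from nephrology". It then states as a hypothesis that "AI-based CPMs combining both clinical and immunological data will lead to improved detection of patients at high risk for graft loss and rejection". None of the three names what AI is to be compared with.

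For the third objective, the Abstract (Methods) says "we will compare the performance of selected AI algorithms, for example, random forest and extreme gradient boosting, as foundation for CPMs". The candidates appear in two more places. In the Introduction, "we will investigate the applicability of tree-based machine learning (ML) algorithms such as random forest (RF) and Extreme Gradient Boosting". In the Discussion (Findings on Using Sensitive Health Data for Development of CPMs), "We will start to investigate the applicability of tree-based models and artificial neural networks as ML methods based on our literature review".

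A conventional prediction model appears once, in Using ML for CPMs: a published multicentre risk score "making use of multivariable Cox regression analysis to predict graft loss in patients". It is cited as related work. The article does not plan to refit it or to use it as a benchmark.

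**The concern.** Words such as added and improved describe a difference between two things. If the stated comparison has AI on both sides, the winner is only the best of the AI models. A simple regression on the same inputs might do as well, and the reader could not tell.

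Published performance figures would not fill the gap. The Limitations section itself says that the centres differ in period, practice and demographics, and Table 1 shows data periods from 1998-2020 at one centre to 2012-2019 at another. A difference from a published figure would mix the effect of the algorithm with differences in case mix, era and endpoint definition.

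The conclusion also has uses. The models are meant to feed patient-specific risk scores and a three-level risk grouping (Patient-Specific Risk Score). An unsupported statement that AI adds value would lend weight to the more complex models.

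**Working it through.** The article gives no performance target, effect size or event rate for this question, so there is no figure to reproduce. The check is to list every planned comparison and ask whether it contains a non-AI reference on the same patients.

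| Where stated | What is compared | Non-AI reference model on the same patients? |
|---|---|---|
| Abstract, Methods | Selected AI algorithms, with random forest and extreme gradient boosting as examples | No |
| Introduction; Discussion | Candidates: tree-based models, then also neural networks | No |
| NephroCAGE FLI | Learning mechanisms: "compare different collaborative learning mechanisms with each other" | No; it concerns how a model is trained across sites |
| Molecular-Genetic Matching | Matching scores and outcome, set against results in the literature | No; the reference is external, and it concerns the matching score rather than the prediction model |
| Using ML for CPMs | Published Cox-based graft-loss score | No; cited only |

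Support vector machines are also called relevant (Introduction; NephroCAGE FLI), but they too are machine-learning candidates.

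Next, what the stated comparison can identify. Let M be a performance measure in the evaluation patients.

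- Stated comparison: M(AI model 1) − M(AI model 2).
- Difference needed for added value over a conventional model: D = M(best AI model) − M(conventional model).

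The first quantity carries no information on M(conventional model), so D is not determined. An illustration with assumed values, none of them from the article, takes an AI model with an area under the ROC curve of 0.80:

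- if regression also reaches 0.80, D = 0.80 − 0.80 = 0.00;
- if regression reaches 0.70, D = 0.80 − 0.70 = 0.10.

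Both cases are compatible with any ranking of random forest against gradient boosting.

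Last, feasibility. A regression on the inputs that the AI models use needs no new data. The cited Cox score is less straightforward as a benchmark. Its features are kidney function, proteinuria, histology and HLA antibody, and Table 2 lists data of these kinds. But Using ML for CPMs describes biopsy as done when rejection or failure occurs, so histology may be present selectively and in connection with the outcome. Kidney function, proteinuria and histology of the graft also do not exist at the time when a pretransplant model would be applied.

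**The case against.** The strongest case against runs as follows.

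**The formal objective is narrower.** The Abstract (Objective) speaks only of developing good prognostic AI models, and comparing candidate algorithms fits that. This stands: a reader might infer that the study cannot meet its third objective, and the documents do not support that. The mismatch is with the aim and hypothesis in the Introduction, which the article also states.

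**Improved need not mean better than regression.** It could mean better than present clinical practice, or better than models without immunological data. This stands as a reading. However, the model comparison stated for the third objective sets up neither of those contrasts, so the reference still has to be named.

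**The study makes other comparisons.** A reader might infer that AI algorithms are the only things compared. That is wrong, as the table above shows. None of the other comparisons supplies the missing reference.

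**The lists are open and the article is condensed.** The algorithms are given as examples, and the site study protocols mentioned under NephroCAGE Data Set are not shown. So nobody can say that a conventional model is ruled out. But the open wording leaves open which AI algorithms are chosen; the category stays AI. The point rests on what the article says, a comparative aim beside a comparison that does not answer it, and not on silence alone. If a site protocol already names a reference model, one sentence would settle the matter.

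**The clinical demonstrator will evaluate the models.** It is planned as an evaluation platform, and the Conclusions call for randomised studies to verify the models. Neither statement describes a non-AI reference for predictive performance.

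**Conclusion.** The point holds in a limited form. As the article is written, the study can rank AI models but cannot support a conclusion that AI adds predictive value over a conventional model. The difference that would show this is not among the stated comparisons, so its size is unknown; the values 0.00 and 0.10 above only illustrate the ambiguity.

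This rests on two assumptions: that added value is meant to include predictive performance, and that no unshown protocol already specifies a reference model. Model development can go ahead regardless. What is affected is the conclusion on added value, so the change should be made before the models are evaluated and any such conclusion is drawn.

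**What to change.** For each endpoint and prediction horizon, add to the comparison in the Abstract (Methods) a penalised logistic (or Cox) regression that uses the same inputs, training patients and evaluation patients as the AI models. Report the paired difference, AI minus regression, in discrimination and in calibration, each with its uncertainty. Base any statement on added value on that difference. If the comparison is not wanted, reword the aim and the hypothesis in the Introduction so that they do not promise it, or name the other reference that is meant.

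A Cox model on the feature groups of the cited score should be an optional secondary benchmark at most. It should be confined to posttransplant graft-loss models and to patients with those measurements available before the time of prediction.

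The cost is protocol wording and a few extra model fits on records already retrieved. Regression should also be easy to handle in the federated setting, since the article says that aggregation is well established for parameter-based approaches and little studied for trees. The downside for the consortium is that the AI result may look less favourable.

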**Results:**

We have received initial funding for NephroCAGE in February 2021. All clinical partners have applied for and received ethics approval as of 2022. The process of exploration of clinical transplant database for variable extraction has started at all the centers in 2022. In total, 8120 patient records have been retrieved as of August 2023. The development and validation of CPMs is ongoing as of 2023.

**Conclusions:**

For the first time, we will (1) combine kidney transplant data from nephrology centers in Germany and Canada, (2) implement federated learning as a foundation to use such real-world transplant data as a basis for the training of CPMs in a privacy-preserving way, and (3) develop a learning software system to investigate population specifics, for example, to understand population heterogeneity, treatment specificities, and individual impact on selected posttransplant outcomes.

**International Registered Report Identifier (IRRID):**

DERR1-10.2196/48892

## Introduction

End-stage kidney disease is growing globally affecting already up to 800 million (10%) people worldwide. Dialysis or kidney transplantation are current options for renal replacement therapy. There are 100,000 dialysis patients in Germany, and 50,000 in Canada [1,2]. In total, 1992 kidney transplantations in Germany and 1673 kidney transplantations in Canada were performed in 2021 [3,4]. Kidney transplantation is the preferred way of renal replacement therapy because it improves the quality of life for patients, extends life expectancy, and saves resources of the health care system [5-7]. However, there is a shortage in donor organs. As a result, in total 6593 patients in Germany and 3060 in Canada were on a waiting list for a suitable donor kidney in 2021 [4,8]. Despite the advances in medicine and improvement of short-term graft survival rates within the first year, long-term graft survival remains stagnant. It shows an attrition rate of approximately 5% annually after the second year resulting in reinitiation of dialysis or transplantation in approximately 50% of patients after 10 years [2,9]. After transplantation, regular follow-up visits especially in the first year are required to detect and prevent fatal outcomes, for example, infections, kidney rejections, or cancer due to over- or underimmunosuppression. Today, nephrologists lack adequate diagnostic measures for assessing and stratifying the individual patient’s risk for posttransplant outcomes, for example, graft failure or rejection [10]. Early detection of patients at high risk would open an additional prevention path: clinicians would have the opportunity to initiate countermeasures earlier and prevent fatal outcomes.

The NephroCAGE consortium was initiated as a strategic lighthouse project supported by the national governments of Germany and Canada to combine medical and technical expertise to build a real-world demonstrator and evaluate the added value of artificial intelligence (AI) in a very specific medical use case from nephrology. It brings together worldwide excellence from transplant centers, academia, and industry from Germany and Canada to join forces as depicted in Figure 1. In total, 4 major clinical kidney transplant centers from both nations have contributed transplants to form the first-of-its-kind international NephroCAGE data set; it forms a longitudinal database of patient-level data from more than 8000 transplant cases over the past 2 decades. The NephroCAGE data set builds the foundation for detailed retrospective data analysis using AI learning techniques and the development of clinical prediction models (CPMs) for prospective identification of posttransplant outcomes of kidney transplant patients. With the help of the CPM predictions, clinicians are expected to improve the quality of care for future patients with kidney disease in Canada, Germany and worldwide by identifying individual patient risks even earlier than possible today.

Immunological differences play a key role in the development of organ rejection reactions, which might lead to graft failure or even graft loss [11,12]. It has been proven that transplant patients sharing compatible serologic human leukocyte antigen (HLA) types with the organ donor have better outcomes compared to patients with incompatible HLA types [13]. Today, only a subset of HLA genes is considered for matching of immunological factors from donors and recipients. The HLA genes located on chromosome six are responsible for encoding of proteins that fold complex structures, so-called epitopes. Today, it is known that checking for HLA compatibility requires in addition to pure genetic information also the assessment of the protein’s 3D structure, which might trigger immunological response. However, current organ allocation algorithms in productive use include only very limited aspects of HLA compatibility, for example, number of mismatches per HLA, to reduce the immunological risk for graft rejection and donor-specific HLA antibodies [14,15]. Recently, new matching methods have been developed to optimize assessment of organ compatibility between donors and recipients incorporating more functional aspects, for example, on biological level and additional molecular specifics [16-18]. Selected methods showed improved precision in predicting immunological risk, some of them being also relevant for organ allocation [11,17,19,20].

The NephroCAGE consortium aims to show advantages of using molecular compatibility for matching of organ donors and recipients. Therefore, we aim to incorporate the latest research results on B cell and T cell epitope matching as a specific feature of our CPMs. Furthermore, we will investigate the applicability of tree-based machine learning (ML) algorithms such as random forest (RF) and Extreme Gradient Boosting as a foundation for the development of CPMs trained on real-world transplant data in nephrology.

Therefore, access to high-quality real-world data is crucial to train and validate high-quality AI models for clinical use. At the same time, clinical data are considered as highly sensitive data, which typically cannot be exposed for training of AI models. The NephroCAGE consortium as the first of its kind has access to multicenter transplant data from 2 nations for the development of AI-based CPMs. One of our hypotheses is that AI-based CPMs combining both clinical and immunological data will lead to improved detection of patients at high risk for graft loss and rejection. Conversely, we will focus on data from patient follow-ups and immunological data, for example, presence of donor-specific antibodies (DSA) for HLA.

Over the past decades, hospitals and transplant centers have developed individual clinical information systems for management of their transplant patient data. As a result, data are scattered across multiple silos using various data formats, which makes multisite research a complex data management task. Thus, the use of standardized data formats, common data dictionaries, shared terminologies and ontologies, and open application programming interfaces (APIs) are required to facilitate the deployment and integration of innovative AI-based solutions into existing clinical IT systems.

Combining data from multiple clinical data sources for development of CPMs traditionally involves complex data preprocessing steps, for example, data harmonization, data transformation, enable semantic interoperability, legal agreements, and data privacy measures [21]. The use of a federated learning infrastructure (FLI) turns around the paradigm of centralized data storage: it enables transfers of algorithms to the data to perform local data processing, thereby keeping data at its original protected location [22,23]. In a decentralized FLI, network nodes located at collaborating transplant centers communicate on a peer-to-peer basis, that is, all network communication is performed between individual network partners without the need for any central instance. This raises the questions about how access control to the nodes is enforced, how CPMs are trained, and how to exchange CPMs between sites. Recently, distributed ledger technology (DLT) emerged to guarantee immutable transactions between untrusted parties. These transactions are kept in a consistent state through automated, algorithm-based consensus-building mechanisms, which eliminates the need for third-party trust enforcement [24]. The aggregation of models in FLIs, that is, the combination of individual CPM versions from different partners, is well-established for parameter-based AI approaches such as neural networks. However, only limited research investigates the aggregation of tree-based or kernel-based AI approaches, such as RFs or support vector machines, which are relevant for the given nephrology use case.

